#### 4.3.3.5. Subgroup analyses

In order to assess if there is evidence of greater treatment efficacy for particular participants, we will repeat the primary analysis separately within subgroups defined by:

- Pandemic status (see Section 4.3.3.2),
- Childhood ADHD status (baseline WURS score  $\geq 46$ ) [19],
- Social support (low vs moderate/high baseline social support):
  - Low social support is defined as a score of 2 or less on at least two of items 1, 2, 3, 5 and 6 of the 7-item ESSI, and a total score of 18 or less [20].

An interaction between subgroup and treatment effect will be used to assess this question, acknowledging that this analysis will have reduced power.

## 4.4. ANALYSIS OF SECONDARY OUTCOMES

Secondary outcomes will be summarised within each treatment group at each time point using means and standard deviations, medians and interquartile ranges, or frequencies and percentages as

appropriate.

The secondary outcomes that are measured only once during follow-up:

- total number of days of self-report MA use,
- longest period of abstinence,
- achieving  $\geq 21$  days abstinence, and
- negative UDS in the 4 weeks prior to week 13,

will be analysed using a generalised linear model to estimate the effect of treatment, adjusting for site and MA use in the 28 days prior to baseline. Multiple imputation will be used to account for the uncertainty due to missing data in these outcomes.

The analyses of secondary outcomes measured longitudinally:

- measures of amphetamine craving, withdrawal, and severity of dependence,
- measures of abuse liability, other drug use, risk behaviour and crime,
- measures of physical and mental health and cognitive and psychosocial functioning,
- treatment satisfaction, and
- medication adherence

(see Section 3.5.2 for a full listing) will follow a similar approach to that described in Section 4.3 for the primary outcome: a mixed model for repeated measures that accounts for within-individual temporal correlations and includes all observations in the modified ITT dataset. For continuous or quasi-continuous outcomes (such as composite scale scores), a linear mixed model may be appropriate, but we will undertake residual checks to assess the suitability of assumptions, and use a generalised linear mixed model with an appropriate distribution for the outcome if necessary. Other types of these outcomes will be analysed with a GLMM with an appropriate distribution, again with residual checks to assess assumptions.

The study retention rate will be summarised at landmark time points (weeks 5, 9, 13 and 19) using a Kaplan–Meier estimate of time to withdrawal from baseline.

The success of blinding will be assessed by cross-tabulating participants' allocated treatment with their predicted treatment at each follow-up time point (weeks 5, 9 and 13). A Chi-squared test at each time point will indicate if there is evidence that an individual's prediction is associated with their allocated treatment.

Tertiary analyses may also be conducted, but none are planned at this stage.

#### **4.5. ANALYSIS OF SAFETY OUTCOMES**

Safety data will be analysed according to the treatment that the participants actually received. Safety analyses will include summaries of the incidence of all adverse events that are possibly or probably treatment related, that occur during the study treatment period or within 30 days of the last dose of study treatment.

All serious adverse events (SAEs) will be listed. In addition, incidence summaries similar to the ones planned for adverse events (AEs) will be performed for the SAEs. Discontinuations due to TEAEs will also be listed, and summarised by treatment group.

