## **2. STUDY OBJECTIVES**

LIMA is a randomised control trial designed with the primary objective to examine the efficacy of oral LDX in reducing methamphetamine use over a 12-week maintenance course of 250mg LDX daily comparing to placebo, and to examine the safety of oral LDX in people who are dependent on methamphetamine.

Secondary objectives are:

- To examine changes in physical and mental health, cognitive and psychosocial functioning and well-being in the study population between those taking oral LDX compared to placebo.
- To examine differences in retention rates in the study population between those taking oral LDX compared to placebo.
- To examine differences in amphetamine cravings, withdrawal and severity of dependence in the study population between those taking oral LDX compared to placebo.
- To examine differences in use of alcohol and other drugs in the study populations between those taking oral LDX compared to placebo.
- To examine differences in bloodborne virus transmission risk behaviour in the study population between those taking oral LDX compared to placebo.
- To examine difference in criminality in the study population between those taking oral LDX compared to placebo.
- To examine the abuse liability profile of oral LDX in people who are dependent on methamphetamine.

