### **3.5.3. Safety endpoint**

The safety endpoints are:

- all AEs and that are possibly or probably treatment related, that occur during the study treatment period or within 30 days of the last dose of study treatment;
- all serious adverse events (SAEs);
- discontinuations due to Treatment Emergent Adverse Events (TEAEs);
- suspected unexpected serious adverse reactions (SUSARs).

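### The SAP specifies adverse event incidence tables only for events judged possibly or probably related, with no all-cause summary of non-serious events by arm

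*SAP*

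**What the plan says.** Section 2 of the SAP sets the primary objective as efficacy "and to examine the safety of oral LDX in people who are dependent on methamphetamine".

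Section 3.5.3 defines the adverse event endpoint as "all AEs and that are possibly or probably treatment related, that occur during the study treatment period", or within 30 days of the last dose. Serious events are a separate endpoint with no causality condition.

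Section 4.5 analyses safety by the treatment actually received. Its one stated rule for adverse event tables is "Safety analyses will include summaries of the incidence of all adverse events that are possibly or probably treatment related", for events "that occur during the study treatment period or within 30 days of the last dose of study treatment". On serious events it says "All serious adverse events (SAEs) will be listed", and adds that "incidence summaries similar to the ones planned for adverse events (AEs) will be performed for the SAEs". Discontinuations due to treatment-emergent events are to be listed and summarised by treatment group.

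The SAP gives no causality scale and does not say who assigns causality.

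**The concern.** In a randomised placebo-controlled trial, the comparison that randomisation protects is all events in one arm against all events in the other. Once events are kept or dropped according to a causality judgement made during follow-up, the comparison is of incidence multiplied by the tendency to attribute. The SAP accepts the general principle elsewhere: its amendment of 1 September 2022 took the withdrawal date out of a subgroup definition because it is post-randomisation information.

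Attribution is also hard in this population. The trial drug is tested as an agonist therapy in people who are using methamphetamine on at least 14 of 28 days at entry. A stimulant-type event can plausibly be put down to the participant's own use, graded unrelated, and so fall outside the only adverse event table that the plan specifies.

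At stake is the non-serious part of a primary safety objective. Efficacy inference, sample size and type I error are not affected.

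**Working it through.** **1. The sections set side by side.** The SAP has no safety figure to reproduce, and the sample size in Section 3.6 plays no part here. The check is which events each section covers.

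| Event class | Section 3.5.3 | Section 4.5 | All-cause summary by arm specified? |
|---|---|---|---|
| Adverse events in general | Filtered, wording garbled | Incidence summary, filtered | No |
| Serious adverse events | All | All listed; incidence summaries modelled on those for adverse events | Unclear |
| Discontinuations due to treatment-emergent events | No filter stated | Listed and summarised by group, no filter stated | Yes, as written |

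The gap is therefore non-serious events that did not lead to discontinuation and were graded below possible. They appear in no specified table.

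**2. The garbled endpoint.** The words "all AEs and that are possibly or probably treatment related" contain a stray conjunction. Deleting it gives a filtered endpoint. Supplying missing words after it could give two endpoints: all events, and the related ones. Section 4.5 does not have this ambiguity and carries only the filtered version, so Section 3.5.3 cannot be used to fill the gap.

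**3. What a filter can do to a comparison.** Let p be the true proportion with an event in an arm and a the share of those events called related. With one event per participant, the filtered table shows p × a. Then:

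- filtered difference = p(LDX) × a(LDX) − p(placebo) × a(placebo)
- filtered ratio = [p(LDX) / p(placebo)] × [a(LDX) / a(placebo)]

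All rates below are assumptions; the SAP gives none.

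| True incidence, LDX vs placebo | Called related, LDX vs placebo | Table shows | Difference (true) | Ratio (true) |
|---|---|---|---|---|
| 30% vs 15% | 50% vs 50% | 0.30 × 0.5 = 15% vs 0.15 × 0.5 = 7.5% | 7.5 points (15) | 2.0 (2.0) |
| 30% vs 15% | 70% vs 30% | 0.30 × 0.7 = 21% vs 0.15 × 0.3 = 4.5% | 16.5 points (15) | 4.7 (2.0) |
| 30% vs 15% | 30% vs 70% | 0.30 × 0.3 = 9% vs 0.15 × 0.7 = 10.5% | −1.5 points (15) | 0.86 (2.0) |
| 20% vs 20% | 70% vs 30% | 0.20 × 0.7 = 14% vs 0.20 × 0.3 = 6% | 8 points (0) | 2.3 (1.0) |

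Equal attribution in both arms leaves the ratio alone and scales the difference by a. Unequal attribution multiplies the ratio by a(LDX) / a(placebo), in whichever direction attribution leans. The second row shows that the difference can come out nearly right by accident while the ratio is far off. An all-cause table does not depend on a at all.

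**The case against.** Several points on the other side have weight.

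- **The wording is not exclusive.** Section 4.5 says what the analyses will include, and an all-cause table could still be produced. That is so, but a table the plan does not name is not a planned table, and Section 3.5.3 appears to filter the endpoint itself.
- **Much is covered elsewhere.** A reader might infer that the plan offers no all-cause safety comparison at all. It does not go that far: serious events are listed without a filter, discontinuations are summarised by group, and Section 3.7 gave the monitoring committee unblinded adverse events with no stated causality limit. Sections 3.5.2 and 4.4 also compare arms on somatic, psychiatric, sleep and withdrawal scales with no attribution step. This narrows the gap. It does not close it, because scale scores are not event counts and cover only what their items ask.
- **Definitely related events.** A reader might infer that such events are left out. The SAP never uses that grade and gives no scale. If the scale stops at probable, nothing is lost. All that can be said is that the SAP does not state how a higher grade, if there is one, would be counted.
- **Blinding.** A reader might take the planned blinding test in Section 4.4 as a sign of biased attribution. It concerns participants' guesses, not those of whoever grades causality. Section 3.4 has clinicians and study personnel blinded, and planning a check is not evidence that blinding failed. The unequal-attribution rows above show what could happen, not what did.
- **The numbers are invented.** They are, and with equal attribution the risk ratio is untouched. They show the mechanism and its range, not an expected bias.

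**Conclusion.** The point holds in a limited form. Sections 4.5 and 3.5.3 tie the specified adverse event summary to a causality judgement, and no all-cause summary of non-serious events by arm is specified, although safety is part of the primary objective. The scope of the serious-event incidence summaries is unclear, because modelling them on the adverse event summaries may or may not bring the filter with it.

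The size cannot be derived from the SAP. On the assumed rates, a true 15-point difference could appear as anything from −1.5 to 16.5 points, and a null effect as 8 points. This rests on attribution below 100% and, for the distorted ratios, on attribution that differs between arms, for which the SAP gives no evidence either way.

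It should be fixed, because the repair is cheap and the weakness is plain. It does not threaten the trial's efficacy conclusions, and serious events and discontinuations are largely protected already.

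**What to change.** In Sections 4.5 and 3.5.3:

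1. Summarise all treatment-emergent adverse events during treatment or within 30 days of the last dose, by treatment received and regardless of attributed causality.
2. Show related events as a subset, defined as any grade at or above possible on the trial's causality scale. This also settles how a grade above probable, if there is one, is counted.
3. State that the incidence summaries of serious events are all-cause.
4. Rewrite the first bullet of Section 3.5.3 so that it matches.

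Risk differences with 95% confidence intervals would be a useful addition but are optional, since Section 4.5 plans descriptive summaries.

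The cost is a few sentences and one more table, assuming that events graded unrelated were recorded, as a filter on grade implies. The existing amendment was approved after unblinding, so this change should likewise be dated and described as made after unblinding. An all-cause table leaves little room for choices that depend on the results.

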## **1.2. STUDY SYNOPSIS**

The LIMA trial [1] is a multi-center double blinded randomised controlled trial designed to evaluate the efficacy of 12 weeks of daily LDX 250mg in reducing methamphetamine use. The target sample is 180 adults with methamphetamine dependence of  $\geq 12$  months who report use of  $\geq 14$  days out of the previous 28. Eligible participants were randomised in a 1:1 ratio to a 15-week intervention consisting of either induction (1 week of 150 mg LDX), maintenance (12 week of 250mg LDX) and reduction (1 week of 50mg LDX, 1 week of 50mg LDX); or placebo. All participants were given access to four sessions of cognitive-behavioural therapy as treatment as usual and received a follow up visit 4 weeks post treatment (week 19).

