## **3.6. SAMPLE SIZE**

Based on the primary outcome measure (days of methamphetamine use out of 28 days), to detect a mean difference of 4.5 days (9 days in control vs. 4.5 days in the LDX group out of 28 days) at week 13 (12 weeks post treatment), assuming a pooled standard deviation (SD) of 9 days (i.e. median effect size  $d=0.5$ ), with over 80% power at a two-sided significance level of 0.05, a sample size of 126 (63 per group) is required. Taking into account an estimated attrition rate of 30%, 180 participants in total (90 per group) need to be randomised.

Prior to unblinding, the observed pooled standard deviation, achieved sample size and attrition rate will be used to recalculate the power of the study to detect the same effect size.

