## **4. STATISTICAL METHODS**

### **4.1. GENERAL CONSIDERATIONS**

#### **4.1.1. Analysis principles**

Summaries of continuous variables will be presented as means and standard deviations, or as medians and interquartile ranges, as appropriate. Categorical variables will be presented as frequencies and percentages.

For comparisons between the two randomised groups, the estimand of interest is the expected difference in outcomes between the prescribed course of LDX and usual care, among participants who receive at least one dose. This corresponds to a modified intention-to-treat (ITT) approach to the analyses, whereby all randomised participants who received at least one dose of the prescribed medication are included according to their allocated arm. That is, withdrawal prior to receiving the first dose will be handled using a principal stratum strategy, on-study death will be handled using a hypothetical strategy, and all other intercurrent events will be handled using a treatment policy strategy.

For each outcome variable, statistical significance will be assessed at the 0.05 level using a two-sided test. In addition to treatment effect estimates and p-values, 95% confidence intervals will be reported to describe uncertainty about the effect of treatment.

No adjustment for multiple testing is planned, as the primary comparison is at a single predefined time point (week 13). However, all results will be reported and interpreted by considering both the strength of the evidence and the consistency of effects across endpoints.

All analyses will be performed using SAS version 9.3 or later, and R 4.0 or later.

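### Adverse event incidence is summarised over a window tied to each participant's last dose, with no account of time at risk, so unequal stopping of treatment can be read as a difference in safety

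*SAP*

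**What the plan says.** Section 3.5.3 defines the adverse event endpoint and section 4.5 its analysis, with the same window in both: events "that occur during the study treatment period or within 30 days of the last dose of study treatment". The planned analysis in section 4.5 is: "Safety analyses will include summaries of the incidence of all adverse events that are possibly or probably treatment related". For serious events, section 3.5.3 sets no window. Section 4.5 lists them all and adds that "incidence summaries similar to the ones planned for adverse events (AEs) will be performed for the SAEs". It also states: "Discontinuations due to TEAEs will also be listed, and summarised by treatment group". Safety data are grouped by treatment actually received.

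Section 4.5 gives no person-time denominator, exposure-adjusted rate, time-to-event method or table of time at risk. It does not define incidence or the study treatment period, and it plans no formal between-arm test of adverse events.

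Elsewhere, section 2 puts safety in the primary objective and differences in retention among the secondary objectives. Section 3.6 assumes 30% attrition, without a split by arm. Section 4.4 summarises retention by Kaplan-Meier. For efficacy, section 4.1.1 says that, apart from withdrawal before the first dose and death, "all other intercurrent events will be handled using a treatment policy strategy".

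**The concern.** A window that ends a fixed number of days after the last dose is shorter for someone who stops early. How long a participant is watched for adverse events is then partly a result of treatment. Incidence summarised side by side over such windows mixes the risk of an event with the time available to observe one.

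The trial sets out to examine whether retention differs by arm, so unequal stopping is a possibility that the safety tables should be able to handle. Without time at risk beside them, a reader cannot tell a lower event risk from a shorter window. The distortion can run either way: it can produce an apparent excess in the better-retained arm, or hide a real excess in the arm that stops earlier.

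The undefined treatment period adds a second problem. The two possible readings give different windows, and so different counts, from the same data.

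**Working it through.** The SAP states no safety figure to reproduce, so the check is a simple model of the window.

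**Inputs from the SAP**
- Planned treatment is 15 weeks (section 1.2): 15 × 7 = 105 days.
- The window runs to 30 days after the last dose (sections 3.5.3 and 4.5). A completer's window is 105 + 30 = 135 days.
- Attrition is 30% overall (section 3.6). It is used here only to centre the assumed stopping rates.

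**Assumptions not in the SAP**
- The adverse event hazard h is constant and the same in both arms.
- The risk of a first event over 135 days is 50%, so h = ln 2 / 135 per day.
- Stopping is unrelated to adverse events, and a share p of an arm stops on one given day.
- The stopping splits average 30% but differ by arm.

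**Formulas**, with w the window of an early stopper
- Mean time at risk = (1 − p) × 135 + p × w
- Incidence = (1 − p) × [1 − exp(−135h)] + p × [1 − exp(−wh)]

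**Reading A: window closes 30 days after the actual last dose.** Stopping at week 6 gives w = 42 + 30 = 72 days, and 1 − exp(−72h) = 0.309.
- 40% stopping: time at risk 0.6 × 135 + 0.4 × 72 = 109.8 days; incidence 0.6 × 0.5 + 0.4 × 0.309 = 42.4%.
- 20% stopping: 0.8 × 135 + 0.2 × 72 = 122.4 days; incidence 0.8 × 0.5 + 0.2 × 0.309 = 46.2%.
- Gap 3.8 points with no true difference.

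**Reading B: the treatment period is the scheduled 15 weeks.** The early stopper stays in the window to day 105, so w = 105 and 1 − exp(−105h) = 0.417.
- 40% stopping: 0.6 × 0.5 + 0.4 × 0.417 = 46.7%.
- 20% stopping: 0.8 × 0.5 + 0.2 × 0.417 = 48.3%.
- Gap 1.7 points (before rounding).

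Other assumed splits, same formulas:

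| Stopping | Reading A | Gap A | Reading B | Gap B |
|---|---|---|---|---|
| 45% v 15%, week 3 (w = 51 in A) | 37.9% v 46.0% | 8.1 | 46.3% v 48.8% | 2.5 |
| 40% v 20%, week 6 (w = 72 in A) | 42.4% v 46.2% | 3.8 | 46.7% v 48.3% | 1.7 |
| 35% v 25%, week 9 (w = 93 in A) | 45.8% v 47.0% | 1.2 | 47.1% v 47.9% | 0.8 |
| 30% v 30%, any one day | equal | 0 | equal | 0 |

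The size also depends on the assumed risk. For 40% versus 20% at week 6, a full-window risk of 20% gives gaps of 1.8 (A) and 0.8 (B) points; a risk of 60% gives 4.3 (A) and 1.8 (B).

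**When the event itself causes the stop.** A simulation with a 40% full-window risk and 30% stopping for other reasons by day 105 gave any-event incidence of 35.7% when half of events ended treatment and 35.6% when none did. The mean window fell from 118 to 111 days. The first event is already counted when it ends treatment; only later or repeat events are lost.

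**The case against.** A window of last dose plus 30 days with as-treated grouping is a common on-treatment convention, and efficacy and safety need not share an estimand. Section 4.5 speaks of summaries that the analyses will include, plans no test, and never calls the incidence crude. Adherence by arm (section 4.2.5) and Kaplan-Meier retention (section 4.4) would let a careful reader see unequal exposure. All serious events are listed, and discontinuations due to adverse events are summarised by arm, which partly guards against an intolerable treatment looking safe.

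Much of this stands. The window is not an error. A reader might infer that the plan is bound to make the earlier-stopping arm look safer. The SAP does not support that: it gives no stopping rates by arm, its retention objective is to examine differences rather than a statement that they are expected, and first-event incidence is not lowered when the event causes the stop. A reader might also take the 30% in section 3.6 as a rate of stopping treatment. It is an attrition rate used to inflate the sample size, and participants lost to the study cannot be observed longer under any window. Nor is the issue confined to non-serious events, since the incidence summaries cover serious ones too.

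The constant hazard is a further weakness. If related events cluster early in treatment, the incidence gap shrinks, and events per person-time would then tend to make the earlier-stopping arm look worse.

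What the objection does not answer is that the arms will be read side by side without a stated time at risk, over a window that the SAP leaves open to two readings. Retention and adherence tables show that exposure differed, but do not correct the event comparison for it.

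**Conclusion.** The point holds as a gap in the safety summary that is cheap to close, not as a demonstrated bias. In the main scenario (40% versus 20% stopping at week 6, 50% full-window risk), the spurious gap is about 4 points if the window follows the actual last dose and about 1.7 points if it covers the scheduled 15 weeks. Across the three unequal splits at that risk, the gap runs from 1.2 to 8.1 points on the first reading and from 0.8 to 2.5 on the second. It is zero when stopping is equal. These sizes rest on assumed splits, an assumed risk, a constant hazard equal in both arms, and stopping unrelated to adverse events. The SAP supplies none of these.

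A tempting stronger conclusion is that the main window should be moved to week 19 so that harm is counted over the same period as benefit. The document does not require that, and a wider window brings in off-drug events that dilute drug-specific signals.

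**What to change.** In sections 3.5.3 and 4.5:

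1. State whether the study treatment period is the scheduled 15 weeks or each participant's own time on drug, and define incidence (for example, the share of dosed participants with at least one event in the window).
2. Keep the planned last dose plus 30 days table as the on-treatment display.
3. Beside it, for adverse events and for the similar summaries of serious events, report by arm the total time at risk and a Kaplan-Meier cumulative incidence of first event, censored at the end of each participant's window or follow-up, whichever comes first. Events per person-time are an alternative, but Kaplan-Meier is preferable because a single rate misleads if related events cluster early.
4. Optionally, show a count of events to week 19 for participants still followed, as a supplement and not a replacement.

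The cost is a short change of wording and a few extra tables. The dosing and withdrawal dates are already needed for the adherence, retention and on-treatment analyses. Kaplan-Meier still assumes that censoring is unrelated to event risk, so it should be read alongside the summary of discontinuations due to adverse events.
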